# A randomized, double-blinded, placebo-controlled clinical trial of duloxetine hydrochloride enteric-coated tablets in the treatment of refractory chronic cough

**DOI:** 10.1186/s12890-023-02575-5

**Published:** 2023-08-02

**Keywords:** Duloxetine, Cough, Prospective studies

## Abstract

**Introduction:**

Refractory cough, a chronic cough with an unclear diagnosis or poor treatment response. The symptoms are often stubborn and persistent, causing serious complications and lowering the patient's quality of life. Cough hypersensitivity syndrome (CHS) is proposed as a potential cause, and reducing sensory nerve hyperresponsiveness is suggested as an effective treatment. However, current drugs have low efficacy and benefit rates and numerous side effects. This trail proposes using duloxetine, a selective 5-HT and norepinephrine reuptake inhibitor, as a potential treatment for refractory cough, which has shown promise in treating pain and depression. Duloxetine may inhibit pain conduction and oxidative stress in peripheral nerves by inhibiting the activity of TRPV1 channels, which play an important role in the peripheral afferent pathway of refractory cough. Meanwhile, the antidepressant effects of duloxetine may also play a role in the treatment of refractory cough.

**Methods and analysis:**

This is a single-center, prospective, randomized, double-blind, and controlled trial. A total of 98 individuals will be randomized in a 1:1 ratio to duloxetine group and placebo control group (starting with 20 mg QD, increasing 20 mg daily until 20 mg TID). After a screening period, the second stage runs from baseline to the 42nd (last) day of treatment, with follow-up visits on the 3rd, 7th, 14th, 21st, 28th, 35th, 42nd and 49th days. The main end-stage observation indicators include objective cough frequency, cough visual analog scale (VAS), cough symptom score, Leicester Cough Questionnaire (LCQ), and cough evaluation test (CET); the secondary end-stage observation indicators include capsaicin cough sensitivity, Patient Health Questionnaire-9 (PHQ-9), Major Depression Inventory (MDI), the Generalized Anxiety Disorder-7 scale (GAD-7), Life Events Scale (LES-32), induced sputum supernatant. The safety measures will be AEs/SAEs, vital signs, liver and kidney function, fecal occult blood test.

**Discussion:**

This study is the first randomized, double-blind, and controlled clinical trial investigating the use of duloxetine in the treatment of refractory coughs. The study aims to provide a high-quality basis for evaluating the efficacy and safety of duloxetine for this condition.

**Trial registration:**

Our study was registered in the Chinese Clinical Trials Register (www.chictr.org.cn/) (ChiCTR2000037429) in 28/08/2020.

**Supplementary Information:**

The online version contains supplementary material available at 10.1186/s12890-023-02575-5.

## Background

Refractory cough is a chronic cough with unclear diagnosis or with a definite diagnosis but poor curative effect. The diagnosis and treatment process recommended by the existing cough guidelines requires that on the basis of careful medical history inquiry and physical examination, necessary auxiliary examinations be selected to identify the cause of chronic cough, and the treatment response to the cause should be determined to confirm or exclude the diagnosis. Sometimes, even after a comprehensive auxiliary examination, the cause of cough cannot be identified, or although the cause can be identified, there is no effective treatment or no good treatment response, resulting in stubborn or persistent cough symptoms. All of the above are refractory coughs [1]. The proportion of refractory cough among cases of chronic cough varies between regions, up to 42%, and our department has found rates of 5–12% [2, 3]. The symptoms of patients with refractory cough are often stubborn and persistent. Severe coughing not only causes headache, chest pain, vomiting, difficulty sleeping, fatigue, cough syncope, urinary incontinence, and other manifestations, as well as complications such as rib fractures, but also makes patients irritable, depressed, and anxious, which seriously lower their quality of life [4, 5]. These patients often seek medical treatment in multiple hospitals, spend huge amounts of money, undergo repeated auxiliary examinations, take various therapeutic drugs indiscriminately, and suffer the risks of drug side effects, causing serious social problems and economic burdens [6].

The cough sensitivity of patients with chronic cough is significantly higher than that of normal people, and it has obvious homology with the basic neurobiological mechanism and pathology of chronic pain [7, 8]. Based on this, Morice et al. proposed the concept of cough hypersensitivity syndrome (CHS), which is defined as a type of disease with chronic cough as the only or most prominent symptom on the basis of cough hypersensitivity [9]. Based on this concept, modulating cough sensitivity has become an important strategy for chronic cough treatment [10, 11]. Much like the mechanism of pain, the occurrence of CHS involves neurogenic inflammation, the transient receptor potential (TRP) family, and other factors. A growing number of researchers believe that both can be caused by sensory hyperactivity (SHR), called hypersensitivity syndrome or neuropathic disease [8]. Appropriately reducing sensory nerve hyperresponsiveness could theoretically be an effective treatment. Neuromodulatory drugs such as gabapentin and P2X3 antagonists, as well as nonpharmacological cough suppressant therapy, have shown a certain effect in reducing cough sensitivity and cough frequency [12–14]. However, the above drugs not only have low efficacy and benefit rates but also have many side effects, such as drowsiness, dizziness, and dysgeusia. Transient receptor potential vanilloid 1 (TRPV1) and transient receptor potential channel subfamily A member 1 (TRPA1) receptor blockers, which have given high hopes to some, have not shown therapeutic effects in recent clinical studies on refractory cough [15, 16] Therefore, patients with refractory cough have few recourses for treatment.

As a selective 5-hydroxytryptamine (5-HT) and norepinephrine (NE) reuptake inhibitor, duloxetine is a strong neuronal 5-HT and NE reuptake inhibitor that has a relatively weak inhibitory effect on dopamine reuptake. It is well tolerated, has few adverse reactions, and has been widely used in pain treatment [17, 18]. *N*-methyl-d-aspartate (NMDA) receptor, gamma-aminobutyric acid (GABA), 5-HT, and NE play important roles in the development of cough and pain and also play relevant roles in the formation of cough hypersensitivity [19, 20]. Theoretically, dual 5-HT and NE reuptake inhibitors could suppress central hypersensitivity by impairing nociceptive pain uploading [21] and could be used in the treatment of refractory cough. Jeyakumar et al. used low-dose amitriptyline to treat refractory cough secondary to vagal pathology induced by viral infection. After 10 days of treatment, the cough frequency, severity, and quality of life of the patients were significantly improved, but most patients stopped treatment due to its side effects, of which the most common were sedation and dry mouth, followed by anxiety, insomnia, dizziness, and weight gain [22]. Duloxetine has no affinity for adrenergic receptors, cholinergic receptors, or histamine receptors, so it causes none of the adverse effects after blockade of α1 and H1 receptors that are common with tricyclic antidepressants such as amitriptyline, giving it good safety and tolerance [23]. The U.S. Food and Drug Administration has approved duloxetine for the treatment of diabetic peripheral neuralgia, fibromyalgia, and chronic musculoskeletal pain. Duloxetine hydrochloride is as effective as traditional antidepressants but is more effective faster and has fewer adverse reactions [24]. Therefore, the analgesic effect of duloxetine may also be applied to the improvement of cough symptoms. Duloxetine may inhibit pain conduction and oxidative stress in peripheral nerves by inhibiting the activity of TRPV1 channels [25], while TRPV1 also plays an important role in the peripheral afferent pathway of refractory cough [26]. Therefore, duloxetine may also reduce peripheral nerve sensitivity in patients with refractory cough by inhibiting the activity of TRPV1 channels.

In addition to possibly improving cough symptoms, the antidepressant effects of 5-HT and NE reuptake inhibitors may also play a role in the treatment of refractory cough. Psychological symptoms are interrelated with cough severity and quality of life. Chronic cough seriously affects the quality of life of patients, causing fatigue, sleep deprivation, and social withdrawal, leading to increased complications of psychiatric disorders such as anxiety and depression. These psychological problems may affect their perception of symptoms and are associated with decreased treatment adherence and slower response to treatment. French et al. found that symptoms of depression, anxiety, and stress also gradually improved when cough symptoms were relieved. They believed that psychological factors, symptom experience, and daily functions interacted and influenced each other, so the authors proposed that intervention on the psychological state may also help improve somatic symptoms and quality of life [27]. As a new type of antidepressant, duloxetine has been used in the treatment of depression and generalized anxiety disorder. It has also shown efficacy in patients with somatic symptom disorders, significantly reducing the level of somatization and functional disability [28]. Therefore, duloxetine can reduce the psychological burden of patients and help improve the symptoms of refractory cough. We propose this study to test the hypothesis that duloxetine has a good therapeutic effect on patients with refractory cough.

### Research objective

The primary objective of this study is to investigate whether duloxetine can improve symptoms in patients with refractory chronic cough.

### Research methods

Through a randomized, double-blinded, placebo-controlled clinical trial, we will explore whether duloxetine hydrochloride enteric-coated tablets can improve the cough symptoms of refractory cough and its underlying mechanisms.

### Research content and methods

(1) We will compare the starting time and effectiveness rate of duloxetine hydrochloride enteric-coated tablets vs. placebo for the reduction of cough symptoms and somatic symptoms in patients with refractory cough. We will also observe whether duloxetine hydrochloride enteric-coated tablets can relieve or control cough symptoms in patients. (2) After discontinuation of duloxetine hydrochloride enteric-coated tablets, the change pattern and effectiveness rate against cough and somatic symptoms of the two groups of patients will be compared, and will determined whether there is a continuation effect of duloxetine hydrochloride enteric-coated tablets after drug discontinuation.

(3) We will compare the changes on the objective cough frequency, cough visual analog scale (VAS), cough symptom score, Leicester Cough Questionnaire (LCQ), cough evaluation test (CET), capsaicin cough sensitivity, Patient Health Questionnaire-9 (PHQ-9), Major Depression Inventory (MDI), the Generalized Anxiety Disorder-7 scale (GAD-7), Life Events Scale (LES-32), and induced sputum supernatant at each time point to explore whether duloxetine acid enteric-coated tablets further improve the quality of life and cough sensitivity of patients with refractory cough.

(4) We will compare the drop-out rate and the completion rate of the treatment course in the two groups of patients to determine whether duloxetine hydrochloride enteric-coated tablets can improve the treatment adherence and success rate of patients.

The first stage is a screening period of up to 3 days and a lead-in period of up to 4 days. The subjects who sign the informed consent form (ICF) will screened, and the qualified subjects will enter the lead-in period. The second stage runs from baseline to the 42nd (last) day of treatment, with follow-up visits on the 3rd, 7th, 14th, 21st, 28th, 35th, and 42nd days to observe the efficacy and safety of the test drugs. The third stage is the follow-up 1 week after treatment ends.

### Inclusion criteria

All patients included in the study must meet all of the following criteria:① Patients or their legal representatives must sign an ICF before any assessment;② 18 years ≤ age ≤ 60 years, male or female;③ Patients with chronic cough whose main symptom is cough, whose cough has lasted for more than 8 weeks, and who have no obvious abnormality in the frontal or lateral chest X-ray. A comprehensive examination according to the diagnostic procedures of chronic cough recommended by China's *Guidelines for Diagnosis and Treatment of Cough (2021)* still cannot identify the cause, or the patient has had no relief despite targeted treatment for known causes.④ Subjects with a cough VAS ≥ 30 mm;

### Exclusion criteria

Screened patients who meet one of the following criteria are not eligible for the study:① Pregnant, breastfeeding women or those who refuse to sign the ICF;② Smoking or having quit smoking ≤ 2 years;③ History of respiratory tract infection within 8 weeks;④ Renal insufficiency, pregnant women, breastfeeding women;⑤ Patients who need to take an angiotensin-converting enzyme inhibitor (ACEI) for a long time;⑥ Other psychiatric disorders or drug dependence;⑦ Patients with hypertension or other cardiovascular system diseases;⑧ The researcher believes that there are other circumstances that make the patient unsuitable for entry into the study.

### Sample size estimation

According to our previous treatment of 11 patients diagnosed with refractory cough with duloxetine hydrochloride enteric-coated tablets at 20 mg TID, seven patients had more than 50% relief from the their cough, and some patients even enjoyed full relief of their cough. The remission rate was 63%. Placebo was 30% effective for refractory cough. According to the estimation formula of the sample size for the comparison of the two sample rates, a two-sided test will be performed at the level of significance of 0.05 and the level of statistical power of 0.8. The number of observed cases needed in each group is 42, so with an estimated loss to follow-up rate of 15%, the number of cases to be observed in each group is 49. A total of 98 cases of refractory cough which seek medical treatment in Tongji Hospital, School of Medicine are needed in the study to detect true results at a statistical significance level of 5%.

### Randomization

According to the random number method set by a computer, each patient is divided into a duloxetine group and a placebo control group.

### Blinding

The trial will be arranged and controlled by the research designer from the aspects of random number generation, allocation of experimental drug codes, experimental drug codes, registration of subjects, recording and evaluation of trial results, research monitoring, and data management. Both investigators and the subjects will be blinded. For the smooth implementation of the double-blinded trial, double-blinded simulation technology will be used to ensure that the provided placebo is identical to the actual duloxetine capsules in terms of dosage form, appearance, properties, smell, etc., but do not contain active ingredients. Both duloxetine capsules and placebo will be labeled with the name "duloxetine," along with the dosage, storage method, and drug number. Unblinding should be done only if the subject has a significant adverse event (SAE).

### Interventions

At baseline, subjects with refractory cough who meet the inclusion and randomization criteria of this study and do not meet the exclusion criteria will be randomly assigned to the experimental drug group or the placebo group, and the experimental group will be given duloxetine hydrochloride enteric-coated tablets 20 mg, TID (starting with 20 mg QD, increasing 20 mg daily until 20 mg TID). The placebo group will receive placebo 20 mg, TID (started with 20 mg QD, increased 20 mg daily until 20 mg TID).

### Criteria for test drug reduction or discontinuation

Reduction or discontinuation of the test drug should be avoided during the trial. However, the investigator will consider dose reduction, suspension, or discontinuation if one of the following occurs:① Occurrence of SAEs related to the test drug;② Adverse reaction (AR) to the tested drugs that cannot be effectively relieved by symptomatic treatment;③ Complications/new onset of other diseases that the test drug may aggravate;④ Significant abnormalities in safety-related laboratory indicators;⑤ Other situations that make investigators believe that dose reduction, suspension, or discontinuation is warranted.

### Combination medication

No combination medication will be tested.

### Prohibited concomitant medication

We will try to avoid combining drugs as much as possible, especially combining medications that have a strong impact on the judgment of the trial results (effectiveness and safety). However, in case of AE, deterioration of the original condition, or complication/new onset of other serious diseases during the trial, the investigator should promptly combine the drugs and actively carry out rescue treatment. If the subject meets the withdrawal criteria, the investigator should make proper arrangements for the subject to withdraw from the trial. All the concomitant medication (including prescription and over-the-counter medications) should be recorded in the case record form (CRF) during the trial, including details of drug name, single dose, frequency of administration, routine of administration, reason for administration, start and end time of administration, etc. If the dosage of concomitant medication changes, it should also be recorded in the CRF. In particular, the combined drug use in the event of an AE should be recorded and reported in a timely way.

### Subject elimination criteria

Subjects can voluntarily withdraw from the trial at any time for any reason, and the investigator can also suspend any subject from participating in the trial for various reasons (mainly including safety issues or breach of protocol). Subjects who have one of the following circumstances shall withdraw from the trial or be deemed to have withdrawn from the trial:① The subjects stopped taking the drug on their own and were unwilling to continue the trial due to poor efficacy or ineffectiveness;② Subjects withdraw their ICF and voluntarily withdraw from the trial;③ Subjects are lost to follow-up.

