### SAE or more severe allergic reactions:

① The subjects are not allowed to continue using the experimental drugs if the investigator and/or monitor thinks it is unsafe and unethical. This is because of the significant abnormalities in safety-related laboratory indicators, the occurrence of SAEs, or more severe allergic reactions associated with the study drug;② The patient goes blind due to SAEs or needs to be resuscitated immediately;③ The patient gets pregnant during the trial;④ It is inappropriate for the patient to continue participating in the trial due to the worsening of the original disease or lack of tolerance during the trial;⑤ If the trial results in complications or the onset of new serious illnesses, such as tuberculosis or tumors, the investigator will deem it necessary to discontinue the trial.

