### Test exit process

① If the patient signs the ICF but is not randomized, the investigator will document the patient's demographic characteristics and reasons for withdrawal and whether AEs or SAEs occurred during the presentation period.② If the subject withdraws from the trial halfway, the investigator should try to complete the inspection and evaluation of various indicators within 2 weeks after withdrawal (preferably before the start of other treatments) as the final follow-up measures. Investigators should contact patients lost to follow-up. For patients who terminate the trial early, the date of the last dose and the reason for early termination should be recorded in the CRF.

Subjects who withdraw from the trial after randomization cannot be replaced. Each randomization number is uniquely associated with each subject and cannot be reused.

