### Security assessment

Examination of AEs and clinical endpoints will begin with randomization and will continue to focus on individual patients until they complete a 14-week follow-up. At each visit, the investigator or designee will conduct a safety assessment and will specifically review the clinical history associated with the occurrence of AEs or SAEs and their causal relationship to the test drug to assess the severity of the AEs. Details of AEs and clinical events will be recorded in the CRF, regardless whether the AE is related to the test drug. All AEs should be tracked for follow-up until the incident is resolved.

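### Patients who leave for intolerance or worsening get one last assessment within 2 weeks, so their day 42 and day 49 main indicators are lost and follow-up rules conflict

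*Protocol article*

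**What the plan says.** Six places in the protocol article bear on what happens when a patient stops treatment.

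- **Subject elimination criteria:** "Subjects who have one of the following circumstances shall withdraw from the trial or be deemed to have withdrawn from the trial". Three circumstances follow: stopping the drug on one's own for poor efficacy and being unwilling to go on, withdrawing consent, and loss to follow-up.
- **SAE or more severe allergic reactions:** item 4 reads "It is inappropriate for the patient to continue participating in the trial due to the worsening of the original disease or lack of tolerance". Item 1 covers serious adverse events (SAEs), laboratory abnormalities and severe allergic reactions. Its wording bars further use of the study drug where the investigator or monitor judges it unsafe.
- **Prohibited concomitant medication:** a subject who meets the withdrawal criteria is to be withdrawn from the trial.
- **Criteria for test drug reduction or discontinuation:** related SAEs, unrelieved adverse reactions and laboratory abnormalities lead to reduction, suspension or discontinuation of the drug. Leaving the trial is not mentioned.
- **Test exit process:** after mid-trial withdrawal, "the investigator should try to complete the inspection and evaluation of various indicators within 2 weeks after withdrawal", preferably before other treatment starts. This counts as the final follow-up.
- **Security assessment:** adverse events (AEs) and clinical endpoints are followed in each patient through a 14-week follow-up, and "All AEs should be tracked for follow-up until the incident is resolved".

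Table 1 ends at Visit 8 (Week 7). Data analysis plans to analyse participants in their assigned group.

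**The concern.** Stopping a drug and leaving a trial are different events. The first ends exposure. The second ends data collection. Where the protocol joins them for intolerance or worsening, outcomes are lost from patients who may be willing to attend, and the reason for the loss is related to both arm and outcome. The comparison at the end of treatment (day 42) and one week later (day 49) then leans on those who tolerated treatment.

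The trial's own aims make this matter. Research content and methods compares drop-out and completion between arms, so drop-out may differ by arm, and it asks whether any effect persists after the drug is stopped. The main indicators are cough frequency, VAS, symptom score, LCQ and CET. An analysis plan can set a rule for a missing yes/no response, but it cannot recover measurements that were never taken.

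The second concern is consistency. Two sites of instruction can send patients with similar events down different follow-up paths, and the stated length of follow-up differs between sections.

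**Working it through.** **1. Does the text end trial participation?**

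- *Worsening or lack of tolerance:* yes, where continuing is judged inappropriate. Item 4 speaks of taking part in the trial, not of taking the drug. The link to the mandatory-withdrawal sentence is inferred from layout: the section title ends in a colon, and the items under Serious violation of the test procedure are fragments that need that sentence to make sense. The rule under Prohibited concomitant medication supports the reading.
- *SAE, severe allergic reaction, laboratory abnormality:* ambiguous. Item 1 and the reduction or discontinuation section speak only of the drug, yet item 1 sits beside the withdrawal list.

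**2. What outcome data remain after exit?** One assessment, no later than 14 days after exit.

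- It can fall on day 42 only if exit is on or after day 42 − 14 = 28.
- It can fall on day 49 only if exit is on or after day 49 − 14 = 35.
- It is one assessment, so it can serve at most one of the two time points.

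Exit before day 28 therefore leaves both time points empty.

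**3. How long is follow-up?** Three lengths are stated: 2 weeks after withdrawal (Test exit process), Week 7 (Table 1) and 14 weeks (Security assessment). Effectiveness evaluation gives control patients 42 days of open treatment after the day 49 visit. That reaches day 49 + 42 = 91, or Week 13, and applies to one arm only, so it does not settle the 14 weeks.

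**4. Scale.** The documents give no withdrawal rate for intolerance or worsening. The only loss figure is the 15% loss to follow-up in Sample size estimation.

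*Reproducing the plan's size.* Inputs: "a two-sided test will be performed at the level of significance of 0.05 and the level of statistical power of 0.8"; response 63% (7 of 11) on duloxetine; "Placebo was 30% effective for refractory cough". With d = 0.33 and mean rate 0.465:

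- n = [1.960 × √(2 × 0.465 × 0.535) + 0.842 × √(0.63 × 0.37 + 0.30 × 0.70)]² / 0.33² = 34.7, so 35 per group.
- With continuity correction: (34.7/4) × [1 + √(1 + 4/(34.7 × 0.33))]² = 40.5, so 41 (stated 42).
- Loss allowance: 41/0.85 = 48.2, so 49; or 42 × 1.15 = 48.3, so 49. The stated 49 per group (98 in total) is reproduced.

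*Illustration.* Assume that the same fraction f leaves in each arm, that leavers are non-responders, and that those who stay respond at 63% and 30%. The difference among stayers is 33 points; among all randomised it is 33 × (1 − f). Power is for the uncorrected two-sided test.

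| f | Duloxetine, all randomised | Placebo, all randomised | Difference (points) | Power, 49 per arm | Power, stayers only |
|---|---|---|---|---|---|
| 10% | 56.7% | 27.0% | 29.7 | 0.86 | 0.89 |
| 15% | 53.6% | 25.5% | 28.1 | 0.82 | 0.87 |
| 20% | 50.4% | 24.0% | 26.4 | 0.78 | 0.85 |
| 25% | 47.3% | 22.5% | 24.8 | 0.74 | 0.82 |

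In whole patients, 7 of 49 leaving gives 0.63 × 42/49 = 54.0% and 0.30 × 42/49 = 25.7%. The difference is 28.3 points, and 33 − 28.3 = 4.7 points separate the two summaries.

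**The case against.** The case against has four parts.

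- **The quoted list does not name intolerance, SAE or worsening.** This stands. Its three items are close to what anyone would call withdrawal from a trial, so the point rests on item 4 of the following section and on reading that section as a continuation.
- **The protocol partly separates drug from trial already.** This stands for SAEs, severe allergic reactions and laboratory abnormalities. A reader might infer that all these patients must leave. The text does not say so; it is unclear.
- **AEs are still followed.** This also stands. A reader might infer that safety observation stops 2 weeks after exit for those who tolerate treatment worst. Security assessment tracks every AE until it resolves, and a site can do a final assessment of indicators and still track AEs. No figure for lost AE observation is supportable. What remains is that the stated lengths do not agree.
- **An analysis plan can count leavers as non-responders, and a full protocol can schedule visits off drug.** This stands in part. Counting leavers as non-responders deals with the 50% response criterion. It does nothing for cough frequency, VAS, LCQ or CET as measured. And the exit rule is stated here, not left out: the 2-week assessment is called final.

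A reader might also apply the 15% loss to the duloxetine arm alone and treat it as intolerance. The documents describe it as loss to follow-up and do not assign it to one arm, so that calculation overstates the gap.

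**Conclusion.** The point holds in limited form. For worsening or lack of tolerance, the article ends trial participation and leaves one attempted assessment within 2 weeks. Day 42 and day 49 main indicators are then missing for reasons related to treatment and outcome, both of them for anyone who leaves before day 28. That undermines the planned analysis by assigned group. For SAEs, severe allergic reactions and laboratory abnormalities, the sections leave open whether the patient leaves the trial. The follow-up lengths of 2 weeks, Week 7 and 14 weeks need reconciling.

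The size cannot be fixed from the documents. The 4.7-point gap assumes 7 of 49 leaving in each arm, none responding, and response of 63% and 30% among those who stay. It shows scale and is not a forecast. Unequal leaving would change it in a way the documents do not let us estimate.

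The conclusion assumes that the section on SAEs and allergic reactions continues the withdrawal list. Nothing here judges which reasons for stopping the drug are right.

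**What to change.** Reconcile Criteria for test drug reduction or discontinuation, Prohibited concomitant medication, the withdrawal sections from Subject elimination criteria to Test exit process, Table 1 and Security assessment:

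1. Define stopping study drug and leaving the trial as separate events. Keep the sponsor's reasons for stopping the drug unchanged.
2. State that a patient who stops the drug, and has neither withdrawn consent nor been lost to follow-up, stays on the Table 1 visits through Visit 8 for the main indicators and AE checks.
3. Make the 2-week assessment additional to those visits.
4. State one follow-up length, and say how AE tracking to resolution relates to it.
5. Record drug status and trial status separately in the case record form, with dates and any other treatment started.

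The cost is wording, a few form fields and some visits that are already scheduled. The downside is that some patients will be assessed off drug and on other treatment, so the analysis must say how those measurements are used.
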